#### Secondary Outcomes

There will be 5 secondary outcomes: (1) presence and access to improved toilets will be assessed using standard questions, while spot observations of toilets will be used to assess maintenance, functionality, and recent use; (2) mental well-being will be measured using The 5-item World Health Organization Well-Being Index (WHO-5); (3) diarrheal disease for all household members will be measured using the WHO definition of three or more loose stools in a 24-hour period, with or without the presence of blood; (4) respiratory illness for children under 5 years will be measured using reported cough and/or difficulty breathing or shortness of breath according to the WHO’s Integrated Management of Childhood illness; and (5) intermediate behavioral antecedents such as empirical expectations (ie, what other people do), normative expectations (ie, what other people think one should do) of prevalence of toilet ownership, exclusive use, and maintenance will be measured using tested indicators (see Multimedia Appendix 2)

### Data Collection

Randomly selected individuals were enrolled for the impact evaluation. They responded to a baseline survey and will be approached to complete a 1-year follow-up survey administered by trained enumerators. The enumerators will be masked to the intervention assignment. However, given the nature of the intervention, they might observe Nam Nalavazhvu intervention products in the household during the follow-up survey.

We enrolled 34 respondents from each cluster and will attempt to reinterview them at endline. We will consider respondents lost to follow-up if any of the following occur: they refuse to participate in the follow-up survey, they relocate elsewhere outside the intervention ward, or the field team is unable to reach them after 3 attempts during data collection. We will replace respondents lost to follow-up by recruiting additional respondents from the sampling frame of the ward. We will ensure 34 respondents per ward at the endline to have adequate power to conduct cross-sectional posttest design analysis.

CSNBD researchers will work with trainers to conduct a 10-day training session prior to each survey round. The training sessions will be conducted in Tamil. Prior to the baseline survey, the instrument was administered to respondents similar to the target group to ensure comprehension. We incorporated feedback to clarify language, framing, answer choices, and administration of the survey. The survey data were collected using personal handheld devices. These electronic surveys were tested to address issues with data capture, skip patterns, and validity checks for each item in a pilot study. Quality assurance steps were taken to improve data accuracy and included regular field-level data checks and dual data capture of objective measures from a subset of households by field supervisors. Researchers from CSNBD also visited the study sites randomly to assess the situation pertaining to the survey. Weekly phone meetings were conducted with the data collection agency to ensure the quality of data.

The implementation partner will collect routine monitoring data to capture information about intervention fidelity and exposure. We will take steps to ensure that they do not involve participants enrolled in the impact evaluation to reduce participant fatigue.

We will conduct 3 rounds of qualitative data collection as part of the process documentation for this study. These will be at 3 months, 6 months, and 1 year after the start of the intervention and will assess participant response, acceptability, and the beliefs about the improved sanitation behavior among respondents in the intervention and counterfactual groups. Trained qualitative researchers will conduct in-depth interviews and focus group discussions with purposively selected respondents in intervention clusters to assess their interaction and experience with the Nam Nalavazhvu intervention. We will use semistructured questionnaires, memos, and note-taking to record observations and will record interviews as required. Verbal consent will be taken before every data collection activity except for observations made in public spaces. Results from this qualitative investigation will be used to interpret the impact of the intervention.

### Data Management

All survey data will be transmitted through secured servers and stored in password-protected folders in the Penn+Box (The University of Pennsylvania). To protect confidentiality, all subjects will be deidentified for analysis. Data will only be accessible to University of Pennsylvania faculty, staff, and data management personnel.

### Statistical Analyses

We will use intention-to-treat analyses to assess the difference in specific outcomes between study arms after exposure to 1 year of the Nam Nalavazhvu intervention. For most of the outcomes, we will use a log-binomial regression model to assess prevalence ratios of postintervention sanitation-related outcomes across intervention groups. We will consider adjusting for variables that were imbalanced between the groups at baseline in adjusted models. We will also use generalized estimating equations with robust SEs to account for the clustering of observations within each cluster (ward). We will use postestimation commands to estimate and report the average marginal effects. We will not adjust *P* values based on multiple comparisons.

In additional analyses, we will use appropriate multivariate models to assess the impact of the intervention on secondary outcomes. Both unadjusted and adjusted effect estimates will be reported for all outcomes. Following the process evaluation findings, if fidelity or intervention quality are found to vary considerably in the trial, we will consider a per-protocol or other appropriate analysis to assess the impact of the Nam Nalavazhvu intervention on our outcomes of interest. The analyses will be conducted by the scientific team ([name]) with statistical software including R (The R Project for Statistical Computing) and Stata (StataCorp).

Qualitative data will be collected until saturation is reached. We will validate key findings using triangulation of data across multiple data sources. We plan to conduct gender-stratified analyses to understand challenges to adoption of exclusive toilet usage.

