### Sample Size

This study is powered to detect differences in the prevalence of exclusive toilet use between study arms. Measuring exclusive use is problematic due to recall and desirability bias. As a result, during our formative research phase, we asked individuals about their defecation place the last time they needed to defecate during 2 rounds of data collection conducted 8 months apart. We incorporated the correlation between these 2 measures in our sample size calculation. We powered our study at 80% based on the prevalence of reported toilet use during last defecation in peri-urban Tamil Nadu (estimated at 64.4% in 2018) and assumed a 10-percentage-point improvement as the minimum important effect [26]. To detect such a minimal effect in exclusive toilet use (given an observed intracluster correlation of 11% and correlation of last use with the one measured in the fall of 2017 of 47.5%) [26], we estimated a requirement of 76 clusters (38 clusters per arm). We require 30 individuals per cluster. Assuming 10% loss to follow-up, we will engage 34 individuals per cluster for a total of 2280 individuals. As we will collect household level toilet usage data, we will have data for more individuals beyond the actual number of respondents.

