## Results

This study completed its baseline survey in January 2020. Endline assessments are planned for July 2021. Results are anticipated to be published by the end of 2022.

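### The 80% power leans on a baseline correlation of 0.475 that the stated post-test analysis does not commit to using; without it, power on the protocol's own inputs is about 70%

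*Protocol article*

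**What the plan says.** All references are to the protocol article.

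- **Sample Size.** Power is set at 80%. Control prevalence of toilet use at last defecation is "estimated at 64.4% in 2018", and the authors "assumed a 10-percentage-point improvement as the minimum important effect". The further inputs are "given an observed intracluster correlation of 11% and correlation of last use with the one measured in the fall of 2017 of 47.5" per cent. The section states that the correlation between the two survey rounds, 8 months apart, was built into the calculation. The result is 38 wards per arm with 30 people analysed per ward.
- **Statistical Analyses.** Postintervention outcomes are compared between arms by log-binomial regression, with generalized estimating equations and robust standard errors for ward clustering. On covariates: "We will consider adjusting for variables that were imbalanced between the groups at baseline in adjusted models". Unadjusted and adjusted estimates will both be reported.
- **Data Collection.** People lost to follow-up are replaced from the ward's sampling frame, and "We will ensure 34 respondents per ward at the endline to have adequate power to conduct cross-sectional posttest design analysis".
- **Results.** "This study completed its baseline survey in January 2020. Endline assessments are planned for July 2021".

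**The concern.** A correlation between an earlier and a later measurement lowers the number of wards only if the analysis uses the earlier measurement. The sample size takes that credit. The analysis text does not commit to earning it: baseline variables enter only if they look imbalanced, and even then adjustment is merely to be considered. Baseline toilet use may well be balanced, since wards were randomized in geographic pairs, and the rule would then give no reason to include it. A post-test comparison of whoever is interviewed at endline gains nothing from the correlation.

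Choosing covariates by observed imbalance is also a weak rule in itself. It ignores how strongly a variable predicts the outcome, and it makes the adjusted model depend on the data.

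At stake is a higher chance of missing an effect that the protocol itself calls the minimum important one, although the variable that would help has been collected in all 76 wards.

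**Working it through.** **Inputs.** From Sample Size: p₁ = 0.644, p₂ = 0.744, difference 0.10, ICC = 0.11, r = 0.475, m = 30 per ward, 38 wards per arm, power 80%. From Data Collection: m = 34 at endline. Assumed, because it is not stated: two-sided alpha of 0.05.

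**1. Reproducing the 38 wards per arm**

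- Individuals per arm without clustering: (1.960 + 0.842)² × (0.644×0.356 + 0.744×0.256) / 0.10² = 329 (unpooled variance). The pooled-variance formula gives 332 and its continuity-corrected form 352.
- Design effect: 1 + 29 × 0.11 = 4.19.
- Factor for baseline adjustment: 1 − 0.475² = 0.774.
- Wards per arm = n × 4.19 / 30, with and without that factor:

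| Formula | Without r | With 1 − r² |
|---|---|---|
| Unpooled | 46.0 | 35.6 |
| Pooled | 46.4 | 35.9 |
| Continuity-corrected | 49.1 | 38.06 |

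The last cell is closest to the stated 38. A change-score factor, 2(1 − r) = 1.05, gives about 48 to 52. An averaging factor, (1 + r)/2, gives 34.3 (pooled) or 36.3 (continuity-corrected).

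**2. Power of the post-test comparison, 38 wards per arm**

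- m = 30: SE = √(0.4197 × 4.19 / 1140) = 0.0393. Power = Φ(0.10/0.0393 − 1.96) = 72.1%. The pooled formula gives 71.7%, and a t reference with 74 df gives 71.0%.
- m = 34: design effect 1 + 33 × 0.11 = 4.63. Power is 73.2% (unpooled), 72.8% (pooled) and 72.1% (t).
- With continuity correction, the form that best matches 38 wards: 68.5% (m = 30) and 69.7% (m = 34).
- Detectable difference at 80% power: about 11 points, against the stated 10.

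Moving from 30 to 34 per ward adds only about one point, because between-ward variation dominates.

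**3. Power with baseline adjustment**

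- r = 0.475 at both ward and individual level, m = 30: 82.5% (unpooled), 82.2% (pooled), 81.5% (t), 79.9% (continuity-corrected).
- r = 0.475 acting only within wards: the design effect becomes 0.89 × 0.774 + 30 × 0.11 = 3.99 instead of 4.19, and power is about 74% (m = 30) or 75% (m = 34).
- r lower than planned: it was measured over 8 months, while January 2020 to July 2021 is 18 months. The documents give no r for that interval. Taking 0.30 to 0.35 as an illustration, power is about 75–79% across m = 30 and 34 (normal or t, no continuity correction).

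**The case against.** **The analysis text does not exclude the baseline outcome.** A reader might infer that the protocol rules out adjusting for it. It does not: it says adjustment will be considered, promises adjusted estimates, and the covariate list may stand in an analysis plan that is not shown. This stands. What remains is that the article does state a covariate rule and a post-test power claim, and neither fits its own sample size.

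**The 1 − r² reading is inferred.** It is tempting to say that 38 can be reached in no other way. Alpha, sidedness and formula are not given, and a one-sided 0.05 test with no correlation gives 36.2 to 39.3 wards per arm, which also brackets 38. But the section says outright that the correlation was used, so the baseline-adjustment reading is the most plausible one.

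**Other features may recover precision.** Randomization was pair-matched within town panchayats, and Sample Size expects toilet-use data on more people than the respondents. Neither gain is quantified or used in the calculation. For illustration, 60 or 85 people per ward without r would give 76.8% or 78.3%, before any loss from correlation within households. That would help an individual-level outcome, not a household-level one.

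**The power claim in Data Collection carries no percentage.** Reading it as a promise of 80% goes beyond the text. It is still hard to call the power adequate when the difference detectable at 80% exceeds the protocol's minimum important effect.

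**The inputs describe a different measure.** Prevalence, ICC and r all concern an individual's last defecation, while the Primary Outcome section defines a household proportion. The documents therefore do not support saying that the primary analysis has 72% power. They support only that the post-test comparison falls short of 80% on the inputs used for sizing.

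**Conclusion.** The mismatch holds. The sample size takes credit for a repeated-measures correlation, and the stated analysis is not committed to using it. On the protocol's inputs, with two-sided alpha of 0.05 assumed, the post-test comparison has about 71–73% power, or 68–70% on the continuity-corrected formula that best matches the stated size. Without the correlation, 80% power would take 46 to 49 wards per arm before rounding up, against 38.

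Baseline adjustment brings power back to about 80% (79.9–82.5% at 30 per ward) only if r = 0.475 holds at ward as well as individual level over about 18 months. Otherwise about 74–79% is more realistic.

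This is a matter of precision. It does not bias the unadjusted intention-to-treat comparison or inflate its type I error. Confidence is high in the mismatch and lower in any exact power figure.

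**What to change.** 1. **Statistical Analyses:** pre-specify that the primary model adjusts for the baseline value of the primary outcome whatever the observed balance. Use the individual's or household's own value plus the ward's baseline prevalence. The ward term also covers replacements who have no baseline record.
2. **Statistical Analyses:** remove observed imbalance as the rule for choosing covariates.
3. **Sample Size:** state alpha, sidedness and formula. Say that the 80% is conditional on this adjustment and on r = 0.475 holding at both levels over about 18 months, with about 74–79% if r is lower or acts only within wards.
4. **Data Collection:** replace the claim of adequate power with the roughly 70–73% that the post-test comparison delivers.
5. In both places, note that the figures are for individual last use and not for the household-level primary outcome.

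The cost is wording and a restated power figure. No extra participants or data are needed, since the outcomes are measured at baseline and the baseline survey covered all 76 wards. The change should be fixed before the endline data are seen.

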### Selection and Assignment of Interventions

Following the baseline data collection, a coinvestigator [name] randomly assigned the wards to counterfactual and intervention arms in a 1:1 ratio, using a computer-generated randomization sequence. The randomization was geographically pair-matched within each town panchayat (Multimedia Appendix 1). Balancing the study arms across geography will allow us to adjust for spatially clustered features or events that may be associated with our outcome. Given the nature of the intervention, the study investigators and the participants will not be masked to the intervention assignment. The data collection team will be masked to the treatment assignment.

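### Wards were randomised in geographic pairs, but the stated analysis clusters on ward only; if paired wards are alike, precision the design has already secured is forgone

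*Protocol article*

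**What the plan says.** Selection and Assignment of Interventions describes a 1:1 allocation of wards: "The randomization was geographically pair-matched within each town panchayat". It gives the purpose: "Balancing the study arms across geography will allow us to adjust for spatially clustered features or events that may be associated with our outcome". With 76 wards this implies 38 pairs.

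Statistical Analyses specifies a log-binomial model by intention to treat, and then: "We will also use generalized estimating equations with robust SEs to account for the clustering of observations within each cluster (ward". On covariates it says: "We will consider adjusting for variables that were imbalanced between the groups at baseline in adjusted models". Neither pair nor town panchayat appears there as a model term, a stratum or a unit of inference.

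Sample Size does not mention the pairing. It works from 80% power, a control prevalence "estimated at 64.4% in 2018", an intracluster correlation of 11%, a correlation of 47.5% with an earlier measurement, and 38 clusters of 30 per arm. On effect size, the investigators "assumed a 10-percentage-point improvement as the minimum important effect".

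**The concern.** The design section creates a means of adjusting for geography, and the analysis section gives it no way into the model. Each pair contributes one ward to each arm, so geography is balanced at ward level by construction, and a rule that looks for baseline imbalance will not select it.

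When the two wards of a pair resemble each other, the arm difference varies less from one possible allocation to another than it would under unrestricted randomisation. A robust variance that treats the 76 wards as independent does not credit that reduction. Intervals are then wider than they need be, and the test rejects too rarely under the null. What is at stake is precision that the randomisation has already secured.

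**Working it through.** **Inputs.** From Sample Size: p1 = 0.644, p2 = 0.744, ICC = 0.11, m = 30 per ward, 38 wards per arm, r = 0.475. Assumed: two-sided alpha 0.05 (not stated), equal ward sizes, 38 complete pairs, risk-difference scale, and a share s of between-ward variance common to a pair. The documents do not give s, so a range is shown.

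**Step 1: reproduce the plan's figure.** The two-proportion formula with continuity correction gives 352 per arm. Design effect: 1 + 29 × 0.11 = 4.19. Baseline factor: 1 − 0.475² = 0.774. Then 352 × 4.19 × 0.774 ≈ 1142 per arm, and 1142/30 = 38.07 clusters, against 38 stated. The figure therefore reproduces as an unpaired design.

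**Step 2: ward-only standard error.**
- Mean binomial variance: v = (0.644 × 0.356 + 0.744 × 0.256)/2 = 0.2099.
- Ward-mean variance: 0.2099 × 4.19/30 = 0.0293.
- SE of the arm difference: √(2 × 0.0293/38) = 0.0393.
- With the baseline factor: 0.0393 × √0.774 = 0.0346.

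**Step 3: effect of pairing.** The correlation between paired ward means is ρ = s × 0.11/(0.11 + 0.89/30) = s × 0.788. The true SE is the ward-only SE × √(1 − ρ), so the overstatement is 1/√(1 − ρ).

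- s = 0.10: ρ = 0.079, ratio 1.04
- s = 0.30: ρ = 0.236, ratio 1.14
- s = 0.50: ρ = 0.394, ratio 1.28

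**Step 4: power for 10 points.** The ward-only test uses t with 74 df and the overstated SE. The paired test uses t with 37 df and the true SE.

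| Share s | With baseline factor: ignoring pairs / using pairs | Without it: ignoring pairs / using pairs |
|---|---|---|
| 0 | 82% / 80% | 71% / 70% |
| 0.10 | 83% / 84% | 72% / 73% |
| 0.30 | 85% / 90% | 74% / 81% |
| 0.50 | 88% / 95% | 76% / 89% |

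Under the null, the ward-only test rejects about 4%, 2% and 1% of the time at shares of 0.10, 0.30 and 0.50. Simulation of ward-level trials agreed with these results (without the baseline factor), and the paired test stayed near 5%.

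**Step 5: two tempting repairs that fall short.**
- Pair terms with uncorrected ward-clustered robust SEs: in the same simulation at s = 0.30 the mean reported SE was 0.0238 against a true 0.0341, about 30% too small. Type I error was near 0.18 at every share tried.
- Town-panchayat indicators with ward-clustered SEs: if the similarity lies between paired wards within a panchayat, a simulation of 38 pairs in 10 panchayats left the SE overstated by about 11% at s = 0.30 and 24% at s = 0.50.

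**The case against.** The strongest reply is that this is a journal article. Exact model terms may stand in an analysis plan that is not shown, and the design section does signal an intention to adjust for geography. The covariate sentence is worded as something to be considered, not as a closed list. So a reader should not infer that the investigators have decided to discard the pairing. What remains is that the article does fix the clustering unit and the covariate rule, and, as fixed, they do not fit the randomisation it describes.

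A reader might also infer that the standard errors are certainly too large and power certainly lost. The documents do not support that. They give no within-pair correlation, and Eligibility Criteria removed adjoining wards and kept at least 1 km between residential units of different clusters, which may make paired wards less alike. With no similarity the ward-only SE is correct and the unpaired test is about 1 point more powerful.

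Nor does this make the trial underpowered against its 80%. The 38 clusters per arm took no credit for pairing, and with the baseline factor the ward-only analysis has 82% to 88% power over shares of 0 to 0.50. The figures near 72% arise only if baseline toilet use is not adjusted for, which is a separate question. Finally, the error is in the conservative direction, so type I error is not inflated.

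**Conclusion.** The point holds as a mismatch between design and stated analysis, with a conditional cost. If pairs share 10%, 30% or 50% of between-ward variance, the gain forgone is about 1, 5 or 7 to 8 points of power with the planned baseline factor, and about 1 to 2, 7 or 13 points without it. This rests on the ICC of 11%, 30 per ward, and pair-shared variance that baseline adjustment does not absorb; if baseline adjustment absorbs some of it, the loss is smaller. The ward-only analysis remains valid. This is a cheap improvement, not a defect that threatens the trial's conclusions.

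**What to change.** State in Statistical Analyses that the primary comparison respects the 38 randomised pairs, and take the confidence interval and the P value from the same pair-level method. Any one of these would do:

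- a paired analysis of ward-level results, with 37 df;
- a permutation test that swaps arms within pairs, with the interval obtained by inverting it;
- the planned regression with standard errors clustered on pair and a small-sample correction, which keeps the prevalence ratio.

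Do not add pair terms while keeping uncorrected ward-clustered robust SEs. If the investigators prefer the ward-only analysis, the section should say so and call it conservative. Settle the choice before endline outcomes are compared by arm, so that it is not made after seeing results.

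The cost is a sentence of text and a few lines of code, since the pairs are known from the randomisation. The downside is fewer degrees of freedom (37 in place of 74), worth about 1 point of power if the matching proves uninformative.
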